### Infant health measurements and interviews

Infants are followed up from birth to 1 year of age. At enrolment and every 3 months anthropometric measurements (age in days, recumbent length, weight, mid-upper arm circumference (after 6 months of age) and head circumference) are collected.

At the end of the follow-up period (age 12–14 months), EED is detected by a combination of the lactulose absorption test^31^ and analysis for faecal myeloperoxidase (MPO) using a commercially available ELISA MPO RUO assay (Alpco, Salem, New Hampshire, USA).

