### Data analysis

#### Objective 1

The prevalence, species composition and genomic diversity of thermotolerant and non-thermotolerant *Campylobacter* spp. in infants, adults, livestock and other reservoirs in the Haramaya woreda will be characterised by descriptive analysis; identification of species and clonal complexes using legacy, core genome and/or whole-genome MLST: phylogenetic analysis,^39^ determination of index of diversity, linkage equilibrium and rarefaction analysis.^40^ Further, the virulome and resistome of the *Campylobacter* isolates will be analysed using comprehensive virulence factors^41^ and antibiotic resistance gene databases.^42^ In addition, a functional profiling of the sequenced genome will be predicted.^43^ Specificity and sensitivity of qPCR and culture methods for detecting *Campylobacter* at the genus and biological group levels will be evaluated using Bayesian modelling of performance characteristics in the absence of a gold standard.^44–46^ Metagenomic sequencing data will be analysed by analysed by latest versions of QIIME V.2,^47^ CCMetagen^48^ and IDseq pipelines.^49^

We will fit a Bayesian two-state Markov model for the temporal process of colonisation and clearance of *Campylobacter* in each infant. The daily transition probabilities between colonisation and clearance will be regressed on time, demographic variables, household characteristics and most recent *Campylobacter* prevalence among samples from livestock, environment and other household members (sampled biannually).

Spatiotemporal effects will be analysed using boosted regression trees^50^ to model the influence of regional environmental variables on the distribution of infections of infants with the *Campylobacter* genus as primary outcome variable. Depending on results, this analysis will also be performed for one or more dominant species. To explore the spatial heterogeneity of effects of covariates on *Campylobacter* infections geographically weighted logistic regression models^51^ will be used.

#### Objective 2

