The primary outcome variable for this objective is the proportion of *Campylobacter* infections in infants to that is attributed to mothers, siblings, livestock and environmental reservoirs based on the genetic population structure of *Campylobacter* sp circulating in these reservoirs. Source attribution will be based on modified Hald^52^ and asymmetric island^53^ models using R packages sourceR^54^ and islandR (https://github.com/jmarshallnz/islandR). We will also explore the use of whole-genome^55 56^ and metagenomic sequencing data^57^ for attribution.

#### Objective 3

Data on sociodemographics, livelihoods, economics, environmental health and sanitation will be analysed descriptively, characterising the context within which the study is occurring. Infant health, including breastfeeding practices, infant diet, vaccination status, use of antibiotics and presence of fever and diarrhoea, will also be described. Women’s empowerment in agriculture will be assessed using five domains of empowerment generated by the Women’s Empowerment in Agriculture Index (WEAI). Within this context, the primary outcome variables (EED biomarkers and nutritional outcome data, including length-for-age Z score and stunting status) will be examined for their associations with the cumulative burden of *Campylobacter* using generalised linear models and generalised estimating equations, respectively. We will adjust for potential confounders including sex, socioeconomic status and kebele residence, and include potential covariates such as breast feeding, infant health, household WaSH conditions, animal ownership, WEAI and food security. To better estimate the cumulative burden of *Campylobacter* we will extract data from the Bayesian Markov model that simulates the underlying daily presence/absence status of any *Campylobacter* sp in symptomatic or asymptomatic children. We will also perform exploratory analysis of associations between the gut microbiome of infants and infection with *Campylobacter* spp, EED biomarkers and stunting.

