Consequent to these challenges, the originally planned follow-up period of 18 months was reduced to 12 months. Further adjustments included the timing and distribution of field team members in communities for data collection, number of samples collected per household, number of anthropometric measurements collected per infant. The protocol in this manuscript includes all changes made until the moment of writing (December 2021), with the caveat that because of increased travel times due to checkpoints and roadblocks, planned EED measurements and end-line long interviews are not yet possible and will be attempted later.

Communication, both between the research team and participants, as well as among members of the research team, has been critical to the adaptive management of the project. Interaction with the study population was facilitated by a Community Advisory Board (CAB), established during formative research and made up of representatives of the participating kebeles.^58^ The CAB met prior to the start of field work and facilitated the research teams’ interactions with local communities. Local CAB members were informed before the team travelled to field sites and were invited into and facilitated critical research-community member communication. This included discussions between the project manager and families who had concerns about ongoing participation in the project.

Realtime information from the CAGED project field teams was instrumental in adapting the project to local norms, expectations and realities, many of which shifted and were reestablished during the COVID-19 pandemic. The field teams shared formal and informal data using a variety of communication platforms. Weekly face-to-face meetings were held for all field teams to discussion and debate approaches to challenges as they occurred; these were followed same day by Zoom-based conversation with Principal Investigators to finalise changes to the weekly plan. The broader team relied heavily on WhatsApp threads for day-to-day communication, field updates or other rapid communication. Zoom-based calls were also used for trainings that targeted the field team, with content ranging from research protocol updates to refresher training on data collection methods, to the importance of COVID-19 vaccines.

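### Objective 3 does not name age or enrolment length-for-age for adjustment but does name infant health; pooling the 3-monthly visits on that set could link cumulative Campylobacter burden to growth spuriously through age

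*Protocol article*

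**What the plan says.** Under Data analysis, Objective 3, the primary outcomes are "EED biomarkers and nutritional outcome data, including length-for-age Z score and stunting status". They "will be examined for their associations with the cumulative burden of *Campylobacter* using generalised linear models and generalised estimating equations, respectively". Read in order, EED biomarkers go to generalised linear models and nutritional outcomes to GEE.

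On adjustment: "We will adjust for potential confounders including sex, socioeconomic status and kebele residence, and include potential covariates such as breast feeding, infant health". The covariate list continues with household WaSH, livestock ownership, the women's empowerment index and food security. That makes nine named variables, in lists that are open by their wording. The same section describes infant health as covering breastfeeding, diet, vaccination, antibiotics, fever and diarrhoea.

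Burden comes from a Bayesian Markov model that "simulates the underlying daily presence/absence status of any *Campylobacter* sp in symptomatic or asymptomatic children". Time does enter that exposure model: "The daily transition probabilities between colonisation and clearance will be regressed on time, demographic variables, household characteristics". No time or age term is named for the outcome models.

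Under Infant health measurements and interviews: "At enrolment and every 3 months anthropometric measurements (age in days, recumbent length, weight", and "Infants are followed up from birth to 1 year of age". EED is placed at 12–14 months, but Adaptive project management reports that "planned EED measurements and end-line long interviews are not yet possible and will be attempted later".

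**The concern.** A running total of colonised days can only rise as an infant ages. If mean length-for-age Z falls over the same months for any reason (diet, other infections, season), a pooled regression of Z on burden without age attributes that fall to Campylobacter. Converting length to a Z score removes the age pattern of the reference population. It does not remove faltering relative to that reference.

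Two further points are separate from this.

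- **Enrolment length-for-age.** It predicts later length and may be related to infection risk. It is measured in the first month of life, before most exposure accrues, but is not named.
- **Infant health.** Fever, diarrhoea and antibiotic use can be consequences of infection; the Introduction itself links enteric infection to symptomatic illness. Adjusting for them can remove part of the effect being estimated.

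At stake is the answer to Objective 3, which the Discussion already says can detect only fairly strong associations.

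**Working it through.** **Plan's own figure.** The article gives no figure for this analysis. Its infant sample size is for prevalence: 1.96² × 0.5 × 0.5 / 0.10² = 96.04, rounded up to 97, against the stated 100. That is consistent and not in dispute. Table 1 sums to 115 infants; with the planned 20% attrition, 115 × 0.80 = 92.

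**Is drift plausible?** The Study setting section gives 45.8% stunting. Assuming SD 1, the mean Z solves Φ(−2 − mean) = 0.458, so the mean is about −1.89. Infants under 2500 g at birth are excluded. Some fall after birth is therefore plausible, but the 45.8% has no age breakdown, so the size of any first-year fall is an assumption.

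**Simulation A.** No true effect; 92 infants; 5 visits; exchangeable GEE with robust SE; 200 replicates per scenario; burden as colonised days.

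| Assumed fall in mean Z over the year | 0.3 | 0.5 | 0.8 |
|---|---|---|---|
| Rejection, no age, all visits | 84% | 100% | 100% |
| Rejection, no age, post-enrolment visits only | 58% | 92% | 100% |
| Rejection, with visit-age terms | 6% | 6.5% | 7% |
| Spurious slope, no age, all visits (Z per 100 colonised days) | −0.15 | −0.24 | −0.39 |

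**Simulation B.** No true effect; 115 infants; visits at 0.5, 3, 6, 9 and 12 months; same estimator and number of replicates. Assumed: between-infant SD 0.9, within-infant SD 0.45, colonisation probability rising with age, and burden unrelated to Z. Models with enrolment Z use post-enrolment outcomes only. Burden is cumulative months colonised.

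| Assumed drift in Z | 0 | −0.25 | −0.5 | −1.0 | −1.4 |
|---|---|---|---|---|---|
| No age | 4.5% | 98% | 100% | 100% | 100% |
| Age | 7.5% | 4.5% | 5% | 5% | 5% |
| Enrolment Z, no age | 7.5% | 87.5% | 100% | 100% | 100% |
| Age and enrolment Z | 6.5% | 4% | 6.5% | 7% | 4.5% |

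The Monte Carlo standard error at a true 5% is √(0.05 × 0.95 / 200) = 1.5 points, so the rates with age are compatible with nominal or slightly above it.

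With burden as a share of days, rejection without age was 4.5% at zero drift and 98.5–100% otherwise; with age, with or without enrolment Z, it was 4–9%. The share-of-days artefact depends on the assumed rise of colonisation with age.

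**What this isolates.** The artefact needs drift and a missing age term. Age removes it; enrolment Z alone does not.

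**Enrolment Z and precision.** If enrolment Z correlates r with later Z, residual variance falls by r². For an assumed r of 0.3–0.6 that is 9–36%, equivalent to 1/(1 − r²) = 1.10–1.56 times as many infants. The article gives no r, so the actual gain is unknown.

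**EED.** Infants enrolled in their first month of life between December 2020 and June 2021 differ in age by about six months. If the deferred tests were done in a short calendar window, age at test would vary by about that much. The article does not give the actual ages.

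**The case against.** The strongest reply is that this is a condensed article with open lists. Nothing excludes age, age in days is recorded at each anthropometric visit, and time is used in the colonisation model. A full analysis plan could well put age or visit in the GEE. This stands: the article does not name age, which is different from ruling it out.

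A reader might go further and infer that the planned analysis will give a false-positive growth association. The article does not support that. The artefact requires several visits pooled, no age or visit term, and a drift in mean length-for-age. The article does not say which visits enter the GEE, whether burden is a total or a share, or what the age-specific Z scores are. With no drift there is no artefact.

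A reader might also infer that all three features feed the age artefact. They do not. Leaving out enrolment length-for-age concerns prior growth and precision, and conditioning on it is one of several defensible formulations. Including infant health tends to attenuate a real effect; it does not create one through age.

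On infant health, the objection is partly right. The term also covers breastfeeding, diet and vaccination, which are plausible confounders, and diarrhoea from other pathogens may confound too. Colonisation in the earlier cross-sectional study was mostly asymptomatic, so the share of effect blocked is unknown. But the open wording does not answer this point, because infant health is a named inclusion.

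**Conclusion.** The point holds in conditional form, at moderate severity. Fitted with the named variables alone to pooled 3-monthly visits, the growth model would be unreliable under even a modest assumed drift: rejection under the null is 58–100% for falls of 0.3–0.8 Z, depending on the visits used, against about 5% with no drift and about 4–7.5% with age added (up to 9% on the share-of-days scale). These rates rest on assumed drift, variances and colonisation pattern, and the two simulations agree in direction and scale.

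The symptom-adjustment point is independent of the simulations and is not quantified. The EED age point depends on when the deferred tests take place. It is not a must-fix, because the lists are open and the study is powered for prevalence and source attribution.

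**What to change.** In Objective 3:

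- Name age at measurement (visit indicators or a smooth term) in every growth model, and age at test in the EED models.
- State the burden scale (total days or share of days), and count only burden accrued before each measurement.
- Use post-enrolment length-for-age as the outcome, with enrolment length-for-age as a pre-exposure covariate.
- Make the model without post-infection fever, diarrhoea and antibiotic use the total-effect analysis. Keep breastfeeding and diet as covariates. Report the symptom-adjusted model as a labelled sensitivity or mediation analysis.

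The cost is wording only, since all these variables are already scheduled for collection. The burden coefficient will have a wider interval once age is in. Leaving symptoms out of the main model may leave some confounding by illness from other pathogens, which the sensitivity model addresses.

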### Patient and public involvement

Patients and/or the public were not involved in the design, or conduct, or reporting, or dissemination plans of this research.

### Adaptive project management

The project site was deliberately selected based on the strength of potential partnerships and the realities of local populations; namely, the high rates of malnutrition among rural smallholder farmers, whose livelihoods employ a mixed livestock/crop system. While it was predictable that this type of environment would present significant logistical, technical and sociocultural constraints to research, it was also essential to examine the fundamental research questions. However, from the onset, the project has experienced additional unexpected challenges. The strength of the research partnership and continuous adaptation to the scientific protocol and data collection procedures have allowed the research to advance, despite changes in the local context.

Numerous unforeseen challenges have presented, perhaps most significantly the COVID-19 pandemic. The project start was delayed from April to December 2020. Extensive COVID-19 safety protocols were developed and continuously adapted to allow the research to advance but to prevent COVID-19 transmission among team members and with the study population. Availability and work/transport dynamics of field and laboratory staff were limited by these necessary measures; examples include weekly screening for COVID-19 symptoms of all team members and associated quarantine procedures, and a policy of having only three field team members as passengers (masked) in a vehicle with the masked driver, with windows down. International travel was completely stopped for over a year. Laboratory analyses were also affected by COVID-19 related global supply chain challenges and prolonged customs clearance procedures, resulting in late delivery of critical equipment and supplies. In addition to COVID-19, other unforeseeable challenges for the field work included the escalating conflict in Tigray, which starting in November 2020 and resulted in a declaration of a national State of Emergency in November 2021, and unusually heavy rains from August to October 2021 resulting in deteriorating road conditions and collapsing bridges. Other more typical setbacks that nonetheless required additional adaptation included reduced availability of the study population during Ramadan (May 2021), personal leave among team members (eg, multiple pregnancies, death of an infant, illness) and concerns about political insecurity surrounding general elections in June 2021.

Consequent to these challenges, the originally planned follow-up period of 18 months was reduced to 12 months. Further adjustments included the timing and distribution of field team members in communities for data collection, number of samples collected per household, number of anthropometric measurements collected per infant. The protocol in this manuscript includes all changes made until the moment of writing (December 2021), with the caveat that because of increased travel times due to checkpoints and roadblocks, planned EED measurements and end-line long interviews are not yet possible and will be attempted later.

Communication, both between the research team and participants, as well as among members of the research team, has been critical to the adaptive management of the project. Interaction with the study population was facilitated by a Community Advisory Board (CAB), established during formative research and made up of representatives of the participating kebeles.^58^ The CAB met prior to the start of field work and facilitated the research teams’ interactions with local communities. Local CAB members were informed before the team travelled to field sites and were invited into and facilitated critical research-community member communication. This included discussions between the project manager and families who had concerns about ongoing participation in the project.

Realtime information from the CAGED project field teams was instrumental in adapting the project to local norms, expectations and realities, many of which shifted and were reestablished during the COVID-19 pandemic. The field teams shared formal and informal data using a variety of communication platforms. Weekly face-to-face meetings were held for all field teams to discussion and debate approaches to challenges as they occurred; these were followed same day by Zoom-based conversation with Principal Investigators to finalise changes to the weekly plan. The broader team relied heavily on WhatsApp threads for day-to-day communication, field updates or other rapid communication. Zoom-based calls were also used for trainings that targeted the field team, with content ranging from research protocol updates to refresher training on data collection methods, to the importance of COVID-19 vaccines.

Data collection has only proceeded because of the research team’s existing partnership, the cultural competency of local team members, and a collective openness to learning and adaptability. In near constant conversation with researchers on the ground about how stakeholders within the study areas were receiving, reacting and engaging the research programme, the team has effectively adapted the scientific protocol from its original design, without jeopardising its scientific integrity, to answer the research questions. This exercise in adaptive management was facilitated by established trust, transparent communication, local project ownership and a firm commitment to the project’s success.

## Discussion

This proposal outlines a detailed research plan for conducting a longitudinal study to understand the complex interactions between livestock and infant health. This will support implementation of the LMP to improve the nutritional status of Ethiopians, while minimising the risk of poor nutritional outcomes associated with EED and impaired linear growth. The knowledge generated in this project will benefit the local population in our study area, who will be provided with knowledge about improving domestic hygiene in relation to management of excreta from livestock and other domestic animals. It also helps the local community and national authorities to understand the determinants of stunting so that they can devise appropriate interventions, which can be evaluated in further studies. Beyond Ethiopia, findings from this study constitute a global public good and will have widespread implications, as the relationship between *Campylobacter* spp, livestock production, EED and infant growth is further explored.

Our study has several limitations. The study has been powered for prevalence estimation and source attribution of *Campylobacter* infections in infants, with a minimum target sample size of 100. This sample size is small to detect associations between nutritional outcomes and putative causal factors such as *Campylobacter* infection. For example, the MAL-ED study enrolled 165–237 infants per study site.^12^ Our sample size will allow us to detect relatively strong associations only. However, the MAL-ED study also demonstrated that the effect of the broad group of non-thermotolerant *Campylobacter* sp on linear growth is stronger than the effect of the well-known thermotolerant species *C. jejuni*. Our ability to detect several non-thermotolerant species separately by qPCR rather than at the group level by an all-inclusive immunoassay allows us to zoom in on the likely small number of species whose effect sizes may be larger than that of the whole group. The study is executed in unprecedented times of a major global pandemic and a major civil conflict in Ethiopia, leading to civic unrest, inflation and increased population mobility. This affects the ability to collect all samples and surveys as planned, resulting in an increased level of missing data. We are implementing several approaches to prevent missingness, including active communication with the CAB members, repeat visits and increasing the number of field workers to accomodate the additional workload and driving times. We will use multiple imputation methods to replace the missing data.

Awareness on the association between infant’s exposure to zoonotic pathogens in livestock faeces and risk of stunting is generally low, constraining initiatives to decrease exposure to these hazards. We aim to create an enabling policy and institutional environment, ensuring that smallholder livestock production and associated risk of EED receive the attention and investment this problem deserves. For example, farmers are unaware of the danger of livestock excreta or the measures they could take to reduce contamination. Health practitioners are unlikely to be equipped to diagnose and treat *Campylobacter* infections, especially those due to long‐term exposure to livestock. Due to lack of awareness, policy-makers and development partners may not prioritise reducing exposure to livestock faeces, in comparison to other food safety, WaSH and broader food security issues. Key strategies for this include the following:

Mapping of relevant stakeholders operating at different levels (eg, academia, policy-makers, research, extension workers).Hosting of stakeholder workshops to discuss on challenges associated with livestock production and associated effects on infant health, and research project proposed solutions and findings to tackle the challenges.Feedback of emerging findings from the research project.Developing and delivery of knowledge mobilisation strategies that respond to local stakeholders’ needs and actively engage them in the uptake and application of research knowledge, using existing government structures to promote safe chicken production and also transfer information and knowledge by training various actors including agricultural extensions, health workers, community health volunteers, etc.

The research findings and lessons from the project will also be documented, synthesised and shared in different ways to inform policy, development practice and to be used as resource material for training farmers, extension workers and future agricultural graduates.

